#### Co-creation

This study has been co-created with Halt professionals, policy officers, and management. They have been closely involved in decision-making concerning integrating the study into their regular working activities and giving their practical view on possible outcomes selected by the researchers based on previous research and the theory of YIM.

#### Study sample

Across both conditions, we aim to include 300 juvenile offenders who are (1) between 12 and 18 years old, (2) referred to Halt by either the police, a prosecutor, a special investigating officer, or a school attendance officer, and (3) required to follow a minimum of three meetings at Halt. Thus, so-called ‘shortened cases’, with only 1 or 2 meetings, will be excluded from participation beyond the first measurement (see Fig. 2).

#### Materials

Our primary outcome, with which we will assess the main intervention effect of YIM on perceived social support and social resourcefulness, will be measured with the Berlin Social Support Scales (BSSS), respectively the subscales ‘Perceived Social Support’ and ‘Support Seeking’ (Schwarzer & Schulz, 2003). All youth and caregiver(s)’ outcomes and measurement points are depicted in Table 1. In Table 2, an overview of measures administered to Halt professionals is presented.

**Table 1 Tab1:** Overview of Youth and Caregiver(s) Measurements

Concepts		Measurement	Informants	# of items	Baseline	Post-test	Follow-up
Demographic factors		Demographics	Y	18–21	*****		
Offense and referral information		Halt’s registration system	HP	-	*****		
Halt intervention characteristics		Halt’s registration system	HP	-	*****		
YIM characteristics		Halt’s registration system	HP	-		*****	
Dynamic risk factors		Halt-SI	HP	-	*****		
Psychosocial problems		Halt-SI SDQ	HP Y	- 20	***** *****		
Prosocial behaviour		SDQ	Y	5	*****	*****	*****
**RESILIENCE FACTORS**:							
**1**	**Quality social network**:						
	1.1 Perceived social support	BSSS, *perceived social support*	Y, C	8	*****	*****	*****
	1.2 Perceived mattering	GMS	Y	5	*****	*****	*****
	1.3 Relatedness to others	BPNS, *relatedness to others*	Y	4	*****	*****	*****
	1.4 Peer network quality	IDF	Y	8	*****	*****	*****
	1.5 Mentor relationship quality	Items relational process YsoR	Y, C Y, C	11 6		*****	*****
**2**	**Social skills**:						
	2.1 Social resourcefulness	BSSS, *support seeking*	Y, C	5	*****	*****	*****
**3**	**Feelings of autonomy and competence**:						
	3.1 Competence satisfaction	BPNS, *competence*	Y	4	*****	*****	*****
	3.2 Autonomy satisfaction	BPNS, *autonomy*	Y	4	*****	*****	*****
**4**	**Attitudes towards delinquency**:		Y		*****	*****	*****
	4.1 Cognitive biases	HIT-Q, *cognitive biases subscales*	Y	39	*****	*****	*****
**5**	**Parental monitoring and family outcomes**						
	5.1 Adolescent disclosure	PMS, *AD*	Y, C	6	*****	*****	*****
	5.2 Parental solicitation 5.3 Family resilience 5.4 Parental stress	PMS, *PS* FES PSS	Y, C C C	6 14 18	***** ***** *****	***** ***** *****	***** ***** *****
**6**	**Commitment to social environment**:						
	6.1 Attachment to school	SCS, *value of school* NSCR, *school form*	Y	11	*****	*****	*****
	6.2 Structured free-time activities	IFTA and TSWF	Y	4–8	*****	*****	*****
**NEED FOR FORMAL SUPPORT**		BSSS, *need for support* IHR	Y, C	8	*****	*****	*****
**REOFFENDING**							
	Self-reported delinquency Youth delinquent behaviour	AHSRD CBCL, *delinquent behaviour*	Y C	17 13	*****	*****	*****

*Note Informants*. *HP* Halt professionals; *C* Caregiver(s); *Y* Youths

*Note Questionnaires. **AD* Adolescent Disclosure; *AHSRD* Add Health Self-Reported Delinquency; *BPNS* Basic Psychological Needs Scale; *BSSS* Berlin Social Support Scale; *CBCL* Child Behaviour Check List; *FES* Family Empowerment Scales; *GMS* General Mattering Scale; *Halt-SI* Risk Assessment Tool Halt; *HIT-Q* How I Think Questionnaire; *IDF* Items Delinquent Friends (Van der Laan & Blom, 2006); *IFTA* and *TSWF * Items Free-Time Activities and Time Spent With Friends (Van der Laan & Blom, 2006); *IHR *Items Halt Research (Ferwerda, 2006); *PMS* Parental Monitoring Scales; *PPI* Peer Pressure Inventory; *PS* Parental Solicitation; *PSS* Parental Stress Scale; *NSCR* Netherlands Institute for the Study of Crime and Law Enforcement; *SCS* School Connectedness Scale; *SDQ* Strength and Difficulties Questionnaire; *WODC* Research and Documentation Centre in the Netherlands; *YsoR* Youth Strength of Relationship; *YSR* Youth Self Report

**Table 2 Tab2:** Overview of Halt Professional Measurements

Concepts	Measurement	Informant	# of items	Before recruitment
Demographic factors	Questionnaire	HP	4	*****
Educational level	Questionnaire	HP	4	*****
Work experience	Questionnaire	HP	2	*****
Outcome Expectancy	OES	HP	3	*****
Personality	QBF	HP	30	*****

*Note Informants. **HP* Halt professionals

*Note Questionnaires. **OES* Outcome Expectancy Scales; *QBF* Quick Big Five

#### Recruitment

Non-YIM-trained Halt professionals will recruit participants for the CAU condition, and YIM-trained professionals will recruit participants for the CAU plus YIM condition. Professionals in both conditions explicitly invite minors (and their caregivers) to participate in research to improve the Halt intervention. This is done verbally during the preliminary conversation when the youth is first registered at Halt and by sending a flyer with core information about the study immediately after this preliminary conversation. A QR-code or link on this flyer refers youth (and their caregivers) to an online consent form (categories: 12–15 years, 16 + years, caregivers). Participants can voluntarily sign up for the study via this route.

**Fig. 2 Fig2:**
[figure not shown]
Participant flow through the study

#### Conditions

**Care as Usual (CAU) condition.** Participants (*N* = 150) will follow the regular Halt intervention implemented by non-YIM-trained Halt professionals, also referred to as *Care as Usual.* Aside from inviting youth to participate, professionals are instructed to follow their regular working activities. During the initial meeting, the content and duration of the Halt intervention (in hours and the number of meetings) are determined by a compulsory screening and risk assessment (i.e., Halt-SI) and the nature of the offence. Tailored to the youths’ needs, the professional then selects activities from five different modules: (1) reflection on one’s behaviour, (2) parental involvement, (3) social skills training, (4) victim-offender reconciliation, and (5) future opportunities. For example, activities in the module ‘social skills training’ are ‘modeling’ and ‘dealing with peer pressure’. It is important to note that victim-offender reconciliation is compulsory for all youth (e.g., writing an apology letter to the victim or providing restitution). After selecting activities, the professional draws up an official contract with agreements on the course of the intervention—signed by the youth. The youth then proceeds to fulfil the activities selected by the professional. Some activities can be done at home, such as writing an apology letter, while others are practised during an intervention meeting with a professional, such as social skills training. Importantly, professionals discuss the completion of each activity with the youth. During the closing meeting, the intervention is completed positively if the youth has complied with all agreements made at the start of the trajectory (Wolthuis & Stentoumi, 2023). If deemed necessary, youth are referred to formal support. The aim is to complete CAU within 100 days. The number of meetings with the professional can vary from one to six, with a minimum intensity of 1 h and a maximum intensity of 20 h. On average, youths follow three meetings: an initial meeting, an intervention meeting, and a closing meeting. The initial meeting is in person, while other meetings can be in person or online. Eighty-five per cent of caregivers are present during the initial and closing meetings and provide support where necessary.

**CAU plus YIM condition.** Participants (*N* = 150) will follow the regular Halt intervention described above in combination with YIM, which can be selected as an activity from the module ‘future opportunities’. If selected, it replaces other Halt activities. During the initial meeting of Halt, professionals in this condition help all youth to identify a mentor by asking the YIM question (i.e., “Who in your environment (an adult, aside from your caregiver(s)) can you turn to if necessary?”). If at least three meetings are necessary, professionals explain what YIM entails and support youth by using the network or YIM assignment, which helps to gain insight into the youth’s network. A positive or negative reaction of the youth can follow. A minimum of four (online) meetings are integrated into Halt’s regular working activities if the youth has identified and nominated a YIM. The first meeting is a conversation between the Halt professional and the YIM. They discuss the reaction of the YIM to being asked by the youth, the help needed by the youth, the YIM’s expectations for the trajectory and the role of the professional. The professional explains that the mentor and the youth have the autonomy to form the trajectory to the youth’s needs and the mentor’s possibilities. The mentor will function as a confidant and ally to the youth in various situations (e.g., listening to the youth or supporting the youth with schoolwork). Mentors are not trained because, in YIM, it is believed that the YIM has all the knowledge and tools to support the youth. The professional has a facilitating role, meaning that they initiate the mentoring trajectory and, if necessary, can be reached for support on the YIM’s initiative. The second meeting officially positions the “YIM”. The youth, caregivers, YIM, and professional discuss each other’s expectations, formulate goals, agree on the support frequency, and plan the evaluation meeting. Thus, the type and frequency of support may vary over youth cases. The mentor can partner with caregiver(s) and professionals by making agreements regarding specific goals (e.g., ensuring a youth goes to school in the case of extreme school absenteeism). Again, the professional takes a facilitating and supportive role. In the third meeting, the professional and the YIM have interim contact to discuss the trajectory and if they can proceed with the evaluation meeting. If this is not the case, they plan another interim contact moment. However, if this is the case, the fourth meeting is a joint evaluative meeting during which the youth, caregivers, YIM, and professional evaluate the goals and agreements made at the start of the trajectory. They also discuss how to proceed and whether it is possible to end Halt’s involvement. If so, this also functions as a closing meeting. Similar to CAU, the completion of Halt is evaluated by the Halt professional, while the completion of YIM is evaluated by all parties (i.e., youth, caregiver(s), YIM and professional). Moreover, the aim is to complete CAU plus YIM within 100 days. Importantly, because YIM meetings are integrated into Halt’s regular working procedures and replace other Halt activities, we expect the same number of meetings between the youth and the professional. However, extra meetings between the youth and their YIM are not uncommon, and the YIM often remains involved after Halt’s involvement has ended.

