
Halt’s population consists of 15,000 juvenile minors each year. Including a representative population of Halt allows for studying how and for whom YIM might work. This knowledge would benefit (Halt) professionals in decision-making on how and when to implement YIM. At the same time, youths who benefit from the approach can be specifically targeted, leading to a tailored approach. Suppose YIM is an effective addition to Halt’s short-term intervention. In that case, YIM can be further implemented within their intervention and potentially more widely within the juvenile justice system, such as juvenile detention centres, even outside the Netherlands. Insight into factors that facilitate or prevent YIM implementation yields specific strategies that impact these boosters or negate these barriers. These challenges and strategies can be considered and adopted by others who aim to implement YIM or a new intervention embedded within an organisation. Overall, this study will contribute to knowledge on whether YIM is a suitable informal mentoring approach for youth within the juvenile delinquency field. Moreover, information on which program elements of YIM work can further strengthen informal mentoring approaches.

This study will investigate the effectiveness of YIM for juvenile delinquents. Subsequently, this study will be able to answer questions considering the working mechanisms and possible boosters and barriers experienced in implementation processes. In conclusion, we will contribute to a further understanding of informal mentoring approaches as a selective prevention strategy within the juvenile delinquency field.

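### The CAU plus YIM arm partly substitutes YIM for usual Halt activities, so the trial cannot isolate the effect of adding YIM to an unchanged Halt package; the stated contrast, Table 1 and the confounding plan should say so.

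*Protocol article*

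**What the plan says.** Under Conditions, participants in the experimental arm "will follow the regular Halt intervention described above in combination with YIM, which can be selected as an activity from the module" on future opportunities. The next sentence reads "If selected, it replaces other Halt activities". The same section later says that YIM meetings are built into regular working procedures and "replace other Halt activities, we expect the same number of meetings between the youth and the professional". It adds that "extra meetings between the youth and their YIM are not uncommon, and the YIM often remains involved after Halt’s involvement has ended".

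The CAU paragraph describes a tailored programme. The professional chooses activities from five modules, and one of these, victim-offender reconciliation, is compulsory for everyone.

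The Abstract and the arm name present the comparison as CAU against CAU plus YIM. The closing part of the Discussion introduces its roll-out remark with "Suppose YIM is an effective addition to" Halt's short-term intervention.

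Two further places bear on the point. Table 1 (Materials) marks "Halt intervention characteristics" at baseline only, whereas YIM characteristics are marked at post-test. The Discussion of challenges lists differences in session numbers and in types of activities among the confounding factors between conditions that will be addressed, without saying how.

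**The concern.** The arm name and the roll-out remark suggest an add-on design, in which both arms receive the same Halt package and one also receives YIM. The replacement rule means that is not what is delivered once YIM is selected. The difference between arms then reflects the effect of YIM less the effect of whatever made way for it.

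This affects how results will be read:

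- A null result under an add-on label invites the conclusion that YIM contributes nothing, when it may match the activities it replaced.
- A positive result shows that Halt with YIM integrated did better than Halt without it. It does not show what YIM would add if nothing were removed.
- If activity types are adjusted for as confounders, the analysis removes part of what assignment to the YIM arm brings about, and the question changes again.

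**Working it through.** No stated figure in the protocol tests this point, so the check sets the passages side by side, counts meetings and gives one illustration.

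**1. Is the displacement material?**

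- CAU: "On average, youths follow three meetings: an initial meeting, an intervention meeting, and a closing meeting". That is 3 youth-professional meetings. Three is also the minimum for trial eligibility (Study sample), so it describes the smallest eligible case.
- YIM arm: "A minimum of four (online) meetings are integrated into Halt’s regular working activities if the youth has identified and nominated a YIM". As described, the first and third are contacts between professional and mentor. The second positions the mentor with the youth present. The fourth is the joint evaluation and can serve as the closing meeting.
- Youth-professional meetings with a positioned mentor: initial + positioning + evaluation/closing = 1 + 1 + 1 = 3.
- Professional contacts of any kind: 1 + 4 = 5 or more, against 3 in the three-meeting CAU case.

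The count of 3 against 3 agrees with the protocol's expectation of equal youth-professional meetings. It also shows where the substitution falls: in a three-meeting case, positioning takes the slot of the only intervention meeting. Longer cases leave more room, and some usual activities are done at home, so the displacement is partial.

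**2. What can be displaced?** Victim-offender reconciliation is compulsory and stays. The candidates are the non-compulsory activities: reflection on behaviour, parental involvement, social skills training, and the rest of the future opportunities module. Several of these relate to outcomes in Table 1, such as parental monitoring, peer network quality and attitudes towards delinquency. The protocol does not say which activities give way, so this list is an inference.

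**3. What does the contrast estimate?** Write Y for the effect of YIM and D for the effect of the displaced activities on the same outcome, and assume that the effects add. Where YIM is selected, the difference between arms is Y − D. An add-on design would estimate Y.

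**4. Illustration only.** Take Y = 0.21, the value in Power Analysis. That figure comes from meta-analyses of formal mentoring on delinquent behaviour and reoffending; it is not an estimate for YIM or for the primary outcomes. Assume D between 0.05 and 0.15, a range with no basis in the document.

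- 0.21 − 0.05 = 0.16
- 0.21 − 0.15 = 0.06
- If D = Y, the expected difference is 0.

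The calculation takes displacement to occur in every case, although the protocol makes it conditional on YIM being selected.

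**5. Will the displaced content be visible?** The content and number of meetings are set at the initial meeting, so a baseline extraction would show the agreed plan and not what was completed. Data collection and procedure says that these characteristics are registered per case in both conditions, but gives no time point. Capture at closing is therefore possible but not stated.

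**6. Confounder or intervention?** Data analyses commits to analysis by assigned condition. Under the replacement rule, a different mix of activities follows from assignment to a YIM-trained professional. Adjusting for that mix does not fit an analysis by assigned condition.

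**The case against.** The strongest reply is that CAU was never a fixed package. It is a menu, YIM is one more item on it, and adding YIM to Halt can fairly mean adding it to the menu. If Halt rolled YIM out, the same replacement would occur, within the same 100-day aim. The Discussion says the study is about effectiveness in daily practice. Read this way, the comparison by assigned condition asks the right policy question. The substitution is disclosed twice, the roll-out sentence is conditional, and the hypotheses in The present study make no claim about addition.

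Most of that stands, and it rules out two stronger readings. A reader might infer that the trial cannot support any roll-out statement. The documents do not bear this out: whether offering YIM within Halt does better than Halt without it is a question the design addresses, subject to non-random allocation. A reader might also infer that the arms are unmatched on contact. Youth-professional meetings are expected to be equal, and the count agrees. The extra mentor contact and professional-mentor contact belong to the mentoring intervention itself.

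The reply does not remove the ambiguity. Disclosure in the arm description does not correct the Abstract, the arm name or the roll-out wording, which readers will rely on. Nor does it help to interpret a null result or settle whether activity type is to be adjusted for.

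**Conclusion.** The point holds in a limited form. The delivered contrast is Halt with YIM integrated and partly replacing usual activities, against usual Halt. The trial can estimate that contrast, with the caution that non-random allocation requires. It cannot separate the effect of adding YIM to an unchanged package, and a null result would not distinguish an inert YIM from one equal to what it displaced.

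The size cannot be derived from the documents. The 0.06 to 0.16 range is an illustration that depends on an assumed displaced effect, on additivity, on displacement in every case and on a mentoring effect borrowed from formal programmes. It should not be cited as an estimate of bias.

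The conclusion itself rests only on the replacement rule, which is explicit. That Table 1 captures only planned content is less certain, because the text on registration sets no time point. The change is worth making: it costs little and improves what can be concluded.

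**What to change.** 1. **Wording.** In the Abstract and the arm description, state the contrast as Halt with YIM partly replacing usual activities versus usual Halt, so that the description and the replacement rule are reconciled. Word the roll-out remark in the Discussion to match, in place of the reference to an addition. The hypotheses need no change on this account.
2. **Measurement.** In Table 1, add an extraction of Halt intervention characteristics (activities completed, meetings held) at case closing in both arms. Report by arm, descriptively, which activities were displaced.
3. **Analysis.** In the Discussion of challenges, say that activity differences brought about by YIM are part of the intervention and will not be adjusted for in the analysis by assigned condition. Differences between cases that precede assignment, such as severity, remain confounders.

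The cost is a narrower claim, some rewording and one later extraction from a register the trial already receives. Neither the delivered programme nor the sample size changes.

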
#### Data collection and procedure

Both recruitment and data collection started on September 1st, 2022. Recruitment will stop after 15 months because researchers strive to complete pre- and post-tests within 18 months. Follow-up measurements can occur up to 24 months after the start of the data collection. Participants will be asked to fill out three questionnaires: before the initial meeting (baseline), 100 days after baseline (post-test), and nine months after baseline (follow-up). After giving consent via the flyer, participants will automatically be referred to the first online questionnaire and instructed to complete it before their initial meeting at Halt. After that, researchers will approach eligible participants for post-test and follow-up measurements (see Fig. 2). All questionnaires will be administered in Dutch and will take approximately 30 min to complete. Participants will receive €7,50 per completed questionnaire; when they complete all questionnaires, they may win AirPods (€130).

Complementary to the questionnaires, we will receive pseudonymised youth case data from Halt’s registration system. Professionals in both conditions will register the characteristics of the Halt intervention (e.g., number of meetings, type of crime) and the risk assessment (i.e., Halt-SI) per youth case. In the CAU plus YIM condition, professionals will additionally register characteristics of YIM (e.g., the reaction of youth to YIM, caregivers’ approval of YIM, and the youth’s relation to the YIM (e.g., uncle, grandmother)). Most importantly, professionals will report the steps they have taken to implement YIM: (1) the YIM question was asked (“Who, an adult aside from your caregiver(s), can you turn to if necessary?”), (2) steps were taken to support youth in identifying and nominating a YIM, such as the network or YIM assignment, and (3) a YIM was positioned in an official meeting with all parties. Note that the third level of implementation is only possible if youths can identify and nominate a mentor.

